### Possible risks and discomfort

The *Lonicerae Japonicae Flos* in Yinqiao Powder contains saponins, which generally had hemolytic effect (Pan et al., 2005; Zhang et al., 2014). However, the saponins contained in *Lonicerae Japonicae Flos* have no or weak hemolytic effect and the potential risk of haemolysis in clinical application is low (Liang et al., 2018). On the other hand, some studies reported that the *Ephedrae Herba* of Maxing Ganshi Decoction contains ephedrine, which consumed in excess can cause a reduction in elimination of adrenaline, resulting in excitation of the sympathetic and central nervous systems (Ou and Wang, 2005; Huang et al., 2017). However, there is no known report on the adverse drug reaction due to *Ephedrae Herba* in the literature related to Maxing Ganshi Decoction (Lin, 2022; Wu et al., 2022). In addition, no severe adverse reaction has been reported in the current literature even though Yinqiao Powder and Maxing Ganshi Decoction are commonly used in the treatment of COVID-19 (Wang et al., 2020c).

### Study visits

#### Screening

Subjects who express interest in our study will be invited to do the screening by video-conference. The electronic informed consent form will be sent to them before the screening. The information about the study will be explained to the participants by our research staff. The eligibility assessment will only be conducted when subjects explicitly indicate that they have read the electronic informed consent form and volunteered to participate in the study at video screening. The written consent form has to be signed after inclusion at the appropriate time. To address exclusion criterion 7 on chronic liver and kidney disease, participants will be screened for chronic liver or kidney disease by asking about their past medical history. If patients’ answer is “Yes”, they will be excluded immediately; if “No”, then we will ask if any blood tests have been done in the past 6 months. If they answer “No”, the participants will be assumed to have no known liver or renal impairment and screening can continue. However, if the answer is “Yes”, then the participants who have blood test reports will be determined based on the results; For those without reports, they will be asked if any medical professional has indicated any abnormalities in liver or kidney function, and those with “Yes” will be excluded, while those with “No” will be screened on the assumption that there is no known liver or kidney impairment. In addition, if patients with symptoms such as jaundice, dark urine and oliguria, which are highly suspicious of liver and kidney impairment, will be excluded and advised to seek medical advice.

#### Baseline randomization (day −1 or 0)

Eligible subjects will be assessed by our registered CMPs via telemedicine in this trial, during which medical history and concomitant medication will be recorded. After stratification, subjects will be randomly assigned in a 1:1 ratio to receive up to 14 days of either modified Yinqiao Powder-Maxing Ganshi Decoction (about 33.4–59.7 g each day) or placebo granules (about 33.4–59.7 g each day). Specifically, the stratified randomisation is based on age (A: “18–49 years old” and B: “50–65 years old”) and the number of vaccination (a: “received 3 or more doses - fulfilling government vaccination requirement” and b: “received 2 doses or less of vaccine - yet to be fully vaccinated”). Subjects will be divided into two groups by age: one group is “18–49 years old” and the other one is “50–65 years old”; then they will be further divided into two groups within the different age group by the numbers of vaccination: one group is “received 3 or more doses of vaccine, and the another is “received 2 doses or less of vaccine”. Four subgroups will be created after stratification and subjects in each subgroup will be randomly assigned to either the treatment or placebo group. The distribution of age and number of vaccinations between the two groups will be roughly comparable after stratified randomisation. The IMP will be prescribed by Registered CMPs and will be sent to patients by delivery service. The current Western medicine treatment can continue during the study period.

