### Sample size and statistical methods

#### Sample size estimation

The primary outcome of the study is the time between starting medication and body temperature returning to normal, i.e., the time to fever resolution after the first treatment. Based on previous studies, we assumed the standard deviation (SD) is 0.7, and the time to fever resolution of half a day (0.5 days) would have clinical significance (Qiu et al., 2020; Chen et al., 2021). Therefore, to detect such a difference between groups, 38 in each group will be needed with a power of 80% and a 5% 2-tail significance level. To allow for possible dropouts during the study period, we inflate this value by 20%, hence a total of 96 patients will be needed for the proposed study and 48 in each group (12 in each sub-group).

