#### Randomization and blinding

A random number table will be generated with a computerized random number generator program. The random allocations will be put into opaque envelopes with sequential study numbers by an independent researcher. Two sets of the envelope will be prepared, one set will be for randomization at the site and another set stored in the investigator’s office for emergency unblinding. Each subject will be assigned with a sequential study number and the corresponding IMP will be prepared according to the allocation by a Chinese medicine pharmacist. In the study, the registered CMP investigators, study subjects and outcome assessors will be kept blind of the allocated intervention.

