#### Statistical analysis

Basic demographic data (gender, age, *etc.*) will be descriptively summarized. Continuous variables are presented as mean ± standard deviation (SD) and categorical variables are presented as ratios. Intra group comparisons between baseline and each visit will be conducted by using paired *t*-test (or Wilcoxon signed rank test). Linear mixed model will be used to compare the outcomes between groups. All statistical tests will be two-sided, and *p* < 0.05 is considered significant difference. The statistical analysis will be done by an independent statistician and all analysis will be conducted by SPSS. If there is a significant difference in the use of western medicines between the treatment and control groups, it will be considered and processed as a covariance in the statistical analysis.

In this study, the subject will be deemed as “per protocol” if they have taken the maximum dose or if they stop until getting negative RAT results on two successive days and the major symptoms subside (defined as oral temperature ≤37.2°C, the score of cough and fatigue ≤1) with ≥85% intake compliance. The intake compliance is calculated by dividing the no. of packs of drugs ingested by either:a) the number of packs of core formula the subject should take daily (daily dose) x the number of days from the day of starting drug intake to the day the drug is stopped according to the criteria (e.g., if the subject should take 4 packs of core formula a day, starts taking drug on 1 January, stops at 8 January according to criteria, and has taken 30 packs, the compliance will be (30/(4 × 8)) x 100%) = 93.75%, with the subject deemed as “per protocol”; orb) daily dose x 14 for all other cases (e.g., if the subject should take 4 packs of core formula a day, starts taking drug in 1 January and stops at 3 January because of adverse events, and has taken 12 packs, the compliance will be (12/(4 × 14)) x 100%) = 21.43%, with subject deemed as not “per protocol”.

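### Randomisation is stratified by age and vaccination, but the stated comparison names no stratum term and its only covariate rule picks a post-randomisation variable

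*Protocol article*

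**What the plan says.** - **Design.** Under Baseline randomization, "the stratified randomisation is based on age (A: “18–49 years old” and B: “50–65 years old”) and the number of vaccination" (3 or more doses against 2 or fewer). Allocation is then made within the strata: "Four subgroups will be created after stratification and subjects in each subgroup will be randomly assigned to either the treatment or placebo group", in a 1:1 ratio. The benefit claimed is balance: "The distribution of age and number of vaccinations between the two groups will be roughly comparable after stratified randomisation".
- **Mechanics.** Under Randomization and blinding, "A random number table will be generated with a computerized random number generator program", with sequentially numbered opaque envelopes. Blocking is neither stated nor ruled out.
- **Size.** Under Sample size estimation, the total of 96 is split as "48 in each group (12 in each sub-group").
- **Analysis.** Under Statistical analysis, "Linear mixed model will be used to compare the outcomes between groups". No fixed effects are listed. The one covariate rule is: "If there is a significant difference in the use of western medicines between the treatment and control groups, it will be considered and processed as" [covariate; the article's word is covariance].
- **Outcomes.** Secondary outcome 9 is the use, and total dosage, of antipyretic, Paxlovid and molnupiravir over 14 days.

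**The concern.** When randomisation is stratified, the analysis normally carries the strata as terms in the model. Otherwise the balance bought by the design is not credited in the standard error. The article describes the stratification at length, but when it turns to covariates it names a different variable.

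That variable is a poor choice for a primary model. Western-medicine use over 14 days arises after treatment starts. The Assessment section ties antipyretic advice to temperature thresholds and defines recovery as normal temperature without antipyretic, so use is bound up with the primary outcome. If the formula shortens fever, it may also reduce antipyretic use, and adjusting for that use would remove or distort part of the effect under study. Entering it only after a significant difference makes this worse, because a difference caused by treatment is what would trigger the adjustment.

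The 12 per sub-group raises a smaller question. Randomising within strata balances the arms in each stratum. It does not make the four strata equal in size.

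**Working it through.** **The plan's own figures.** Inputs from Sample size estimation: difference 0.5 days, SD 0.7, 80% power, two-sided 5%, 38 per group, 20% dropout.

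- n per group = 2 × (1.96 + 0.84)² × 0.7² / 0.5² = 30.8, so 31 (32 with the t distribution). The stated 38 is not reproduced. At 38 per group these inputs give about 87% power. This does not bear on the present point, except that power below starts near 87% and not at 80%.
- 38 / (1 − 0.20) = 47.5, so 48 per group and 96 in total: reproduced.
- 48 / 4 strata = 12. The sub-group figure is this division. The article describes no recruitment rule that would produce it.

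**Effect of leaving out the strata.** The share of outcome variance explained by the strata (R²) is not in the article. I assume 0 to 0.20.

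Unadjusted standard error at 38 per group: 0.7 × √(2/38) = 0.161. With balanced allocation within strata, the true standard error of the difference is 0.161 × √(1 − R²):

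- R² 0.05: 0.161 × 0.975 = 0.157
- R² 0.10: 0.161 × 0.949 = 0.152
- R² 0.20: 0.161 × 0.894 = 0.144

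The unadjusted test divides by 0.161 throughout, so its actual size is about 2 × [1 − Φ(1.96 / √(1 − R²))]: 4.4%, 3.9% and 2.8%.

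A simulation checks this: four equal strata, 38 per arm, one normally distributed value per patient, 20,000 runs per setting. It compares a model with treatment only and a model with treatment plus stratum indicators. With one value per patient, a linear model stands in for the article's linear mixed model.

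| Allocation within strata | R² | Type I error, unadjusted | Type I error, adjusted | Power, unadjusted | Power, adjusted |
|---|---|---|---|---|---|
| Balanced | 0 | 5.1% | 5.1% | 86.5% | 86.5% |
| Balanced | 0.05 | 4.5% | 5.0% | 87.2% | 88.2% |
| Balanced | 0.10 | 4.0% | 5.1% | 87.5% | 89.6% |
| Balanced | 0.20 | 2.9% | 4.9% | 88.8% | 92.6% |
| Simple | 0 | 5.0% | 5.3% | 86.8% | 85.1% |
| Simple | 0.05 | 5.2% | 4.9% | 86.4% | 86.9% |
| Simple | 0.10 | 5.0% | 4.9% | 86.5% | 88.5% |
| Simple | 0.20 | 5.0% | 4.9% | 86.1% | 91.4% |

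With balanced allocation, adjustment gains 1.0, 2.1 and 3.8 points at R² 0.05, 0.10 and 0.20. With simple randomisation the unadjusted test holds its 5%, and adjustment gains 0.5, 2.0 and 5.3 points. If the strata are not prognostic, omitting them loses nothing. Adjusting is then free under balanced allocation and costs about 1.7 points under simple randomisation.

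**The covariate rule.** Setting Statistical analysis beside Secondary outcomes shows that the candidate covariate is measured as an outcome over 14 days. The resulting bias cannot be sized, because the article gives no expected usage and no link between usage and time to recovery.

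**The case against.** The article nowhere says that the strata will be left out. It lists no fixed effects at all, and an analysis plan that is not shown may well supply them. This stands: a missing stratum term alone would not be a finding. What remains is that the article does fix a covariate rule, and that rule names a post-randomisation variable and neither design factor.

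A reader might infer that the standard errors are certainly wrong, or that false positives are inflated. The documents support neither. A mismatch needs both balanced allocation within strata and prognostic strata. No blocking is stated, the 12 per sub-group only hints at fixed cells, and the stated reason for stratifying is balance, not prognosis. Where the mismatch does occur, it is conservative.

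A reader might also infer from the 12 per sub-group that recruitment is capped by stratum or that the strata will be compared separately. No cap is described, the Study population section recruits those who are eligible, and no per-stratum comparison is planned. The figure needs explaining and shows no more than that.

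Finally, concomitant medication is recorded at screening, and adjusting for use before randomisation would be unobjectionable. But the rule is not limited to that, and the Discussion treats recorded use of other medication as an outcome.

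**Conclusion.** The point holds in a limited form, as an improvement the plan should make. The firmer part is the covariate rule: as written, a variable that treatment can affect may enter the comparison after a significance test. Its direction and size cannot be given.

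Leaving out the strata matters less. Over the assumed R² of 0.05 to 0.20, at SD 0.7 and 38 per arm, the price under balanced allocation is a test running at about 4.5% down to 3% and a loss of about 1 to 4 points of power. Under simple randomisation only precision is lost. These figures rest on equal strata, normal errors and complete data.

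**What to change.** Three changes to the text, settled before unblinding:

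1. In Statistical analysis, state that the primary model includes age group and vaccination group as used in the randomisation. Baseline oral temperature, already taken at screening, may be added as an option.
2. Take western-medicine use out of the primary model. Report it as secondary outcome 9 and, if wanted, in a prespecified sensitivity analysis carried out whether or not the arms differ significantly.
3. In Sample size estimation, replace the 12 per sub-group with a statement that stratum sizes follow recruitment. If a quota is intended, state it.

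It would also help to say whether allocation within strata is blocked, since that decides which half of the table applies. The cost is a few sentences, with no new data and no change to the sample size.

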#### Follow-up assessment (Days 7, 14) and end-of-study assessment (Day 35)

Subjects will have video consultation on day 7 (±1 day) and day 14 (±1 day) and post treatment follow up at day 35 (±1 day) (Table 1). Subjects are required to measure their body temperature and oxygen saturation twice daily; conduct RATs, clinical symptom score measurement and tongue image capture once daily during the day 0–14 (or until the body temperature returns to normal for 24 h/the day the RAT is negative for 24 consecutive hours, whichever is later). Subjects also need to score their symptoms and capture their own tongue image at day 35. All subjects are required to keep a daily record on their body temperature, oxygen saturation, result of RATs, symptom scores, IMP compliance and adverse events. A direct telephone line will be provided so that subjects can report any adverse event during office hours. The subjects will be recommended to attend Emergency Department at the nearest hospital beyond office hours if deemed necessary. In order to ensure compliance, supermarket shopping vouchers worth 300 Hong Kong dollars will be provided to all subjects by registered mail upon completion of the study. Compliance with medication will be assessed by asking subjects about their remaining medication on the remote assessment (days 7, 14 and 35) and by patient diaries completed by the subjects which will be sent back to the research team after the day 35 assessment.

**TABLE 1 T1:** Study schedule.

Items	Screening	Treatment period			End of study visit
	−1 to 0 days	Day 0	Day 7 (±1 days)	Day 14 (±1 days)	Day 35 (±1 days)
Explicit consent on virtual screening	X				
Eligibility	X				
Medical consultation and assessment	X		X	X	X
Medical history	X				
Concomitant medication	X		X	X	X
AE/SAE assessment			X	X	X
Prescription and dispensing of IMP	X				
Medication		X (Max: 14 days)			
Body temperature and oxygen saturation measurement, RAT and tongue image taken		X (14 days or until recovery)			X
Subjects’ daily record for study		X			

### Study schedule

Please see Table 1.

### Study outcomes

#### Assessment

1. The time between starting medication and body temperature returning to normal and the recurrence rate of fever after momentary recovery. Each subject will be issued with the same type of oral thermometer for measurement at 9 a.m. (±2 h) and 9 p.m. (±2 h) daily, with at least 12 h between each measurement. Normal oral temperature is defined as equal to or below 37.2°C. Temperature recovery time is defined as the total number of days between medication starting date and the date of “normal oral temperature for 24 h without antipyretic” (both days inclusive). Subjects are required to measure the temperature until day 14 or on the day when the temperature has remained normal for 24 h, whichever is later.2. The negative rate of RATs at day 14 and negative conversion time. Each subject will be issued with the same type of RAT kits which can be used for at least 14 days for testing at 9 a.m. (±2 h) each day, with at least 24 h between each test. Negative conversion time is defined as the total number of days between the medication starting date and the date of securing two successive negative RAT results (both days inclusive). Subjects were required to undergo testing until day 14 or the day when two successive negative RAT results at least 24 h apart are obtained, whichever is later.3. The remission rate at day 14 and remission time of major symptoms.4. The disappearance rates at day 14 and disappearance time of symptoms. Subjects are required to record the status of their symptoms including major clinical symptoms daily at 9 p.m. (±2 h). Except for fever which is marked as ‘No’ or ‘Yes’ according to whether the oral temperature exceeds 37.2°C, other symptoms will be graded on a scale of 0–4 from “None”, “Mild”, “Moderate”, “Severe” and “Very Severe” depending on the actual feelings of the subject (“None” means the symptom is not present, “Mild” means the symptom is present but does not interfere with daily activities; “Moderate” means the symptom is present and slightly interferes with daily activities; “Severe” means the symptom is present and most daily activities cannot be done; “Very Severe” means the symptom is present and interferes with all daily activities). Major clinical symptoms include fever, cough and fatigue. Remission is defined as oral temperature ≤37.2°C, cough and fatigue score ≤1; disappearance is defined as the symptom being present at day 0 (score >0) but the symptom score is 0 at the date of recording.5. All-cause mortality at the 21st day after stopping the medication.6. Incidence of the progression to severe or critical illness during the trial. The all-cause mortality at the 21st day after stopping the medication and the incidence of the progression to severe or critical illness during the trial will be confirmed by communication with the subjects and/or other related person(s) or checking their medical record in the Hospital Authority. The definitions of severe and critical illness are based on the related definitions of “Coronavirus disease 2019 (COVID-19) Treatment Guidelines” published by National Institutes of Health (severe illness: oxygen saturation in the indoor environment of sea level <94%, oxygenation index [PaO2/FiO2] < 300 mmHg, respiratory frequency >30 breaths/min, lung infiltrates >50%; critical illness: respiratory failure, septic shock, and/or multiorgan dysfunction or failure).7. Utilization rates of antipyretic, Paxlovid and molnupiravir within 14 days and the total dosage(s) of the drug(s) used. In this study, subjects are allowed to take western medicines prescribed for the treatment of COVID-19 under the current guidelines of the Hong Kong Hospital Authority with at least 2 h’ gap between Chinese and western medicines. If oral temperature >39.0°C and continues over 4 h; or the oral temperature >39.5°C, the patient is advised to take antipyretic (paracetamol is recommended as a priority) for acute treatment. Patients need to record the amount and time of the drug(s) used.8. Oxygen saturation. For safety reasons, each subject will be issued with the same type of pulse oximeter for measurement at 9 a.m. (±2 h) and 9 p.m. (±2 h) daily, or whenever the subject decides it is necessary. If the reading is less than 94%, the patient is considered to have severe illness and has reached the end point of the study and is recommended to seek medical attention immediately. Subjects are required to measure their oxygen saturation at rest until day 14 or the time of body temperature returning to normal (continuing for 24 h) or the negative conversion time (2 successive negative RAT results), whichever is later.

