
### Primary outcome

The time between starting medication and body temperature returning to normal (oral temperature 37.2°C and maintain 24 hours).

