### Secondary outcomes

1. The recurrence rate of fever after momentary recovery: the incidence of fever recurrence (oral temperature > 37.2°C) within 24 hours after the patient’s temperature has normalized after treatment;2. The negative rate of RATs at day 14 and the negative conversion time (two successive negative RATs result with at least 24 hours interval);3. The remission rate of major symptoms at day 14 (oral temperature ≤ 37.2°C, score of cough and fatigue ≤ 1 (“None”, “Mild”, “Moderate”, “Severe” and “Very severe” were marked as 0 to 4 450 respectively), and continues 24 hours);4. Time of major symptoms remission: time from the start of treatment to symptoms remission (definition of symptoms remission: oral temperature ≤ 37.2°C, cough and fatigue score ≤ 1 and lasting at least 24 hours);5. The disappearance rates at day 14 and disappearance time of symptoms: the disappearance rates and time of individual symptoms of mild and moderate COVID-19 within 14 days (time defined as the period between starting medication and symptom disappearance); 6. The rate of patients whose oxygen saturation had gone below< 94% after intake of drugIMP, measured at day 14;7. Incidence of the progression to severe or critical illness during the trial;8. All-cause mortality at the 21st day after stopping the medication;9. Utilization rates of antipyretic, Paxlovid and molnupiravir within 14 days and the total dosage(s) of the drug(s) used.

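### Fever recovery is counted in whole dates although temperature is read twice daily for a 0.5-day target, and the minimum reading gaps leave no slack for the ±2 h windows

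*Protocol article*

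**What the plan says.** All references are to the protocol article.

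- **Primary outcome** names the endpoint as "The time between starting medication and body temperature returning to normal", sustained for 24 hours, and gives no unit.
- **Assessment, item 1** supplies the unit: "Temperature recovery time is defined as the total number of days between medication starting date and the date of" 24 h of normal oral temperature without antipyretic, with both end dates counted. The result is a whole number.
- The same item schedules temperature at "9 a.m. (±2 h) and 9 p.m. (±2 h) daily, with at least 12 h between each measurement".
- **Assessment, item 2** treats the RAT outcome in the same way: "Negative conversion time is defined as the total number of days between the medication starting date and the date of securing two successive negative RAT". Here too, both end dates are counted. Tests are scheduled "for testing at 9 a.m. (±2 h) each day, with at least 24 h between each test".
- **Secondary outcomes, item 2** builds the gap into the RAT outcome itself: "two successive negative RATs result with at least 24 hours interval".
- **Sample size estimation** assumes an SD of 0.7 and holds that "the time to fever resolution of half a day (0.5 days) would have clinical significance". It arrives at 38 per group for 80% power at two-sided 5%, and 48 per group (96 in total) after a 20% allowance for dropout.

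**The concern.** There are two separate points.

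**Resolution of the primary outcome.** The endpoint moves in steps of one day, twice the difference the trial is meant to detect, while the diary holds readings about every 12 h. A patient who takes the first dose at 10:00 and one who takes it at 22:00 on the same date both start at day 1. The medication is delivered and taken in morning and evening portions, so such spread is plausible. Rounding of this kind adds variance to a small trial.

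**Gaps against windows.** The 9 a.m. and 9 p.m. slots are exactly 12 h apart, and successive 9 a.m. RATs exactly 24 h apart. The required minimum equals the nominal spacing, so the ±2 h tolerance works in one direction only: each reading must be at the same clock time as the last or later. For RATs, a breach changes the recorded outcome.

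**Working it through.** **1. The plan's own sample size.** Inputs: difference 0.5 day, SD 0.7 (read as days), 80% power, two-sided 5%.

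n = 2 × (1.960 + 0.842)² × 0.7² / 0.5² = 30.8, so 31 per group; 32 with the t distribution. The stated 38 does not follow from the stated inputs and is larger. The dropout step does reproduce: 38 / 0.8 = 47.5, so 48 per group and 96 in total.

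**2. Variance added by rounding**, if 0.7 is the SD of the exact time (0.7² = 0.49). A grid of width w adds about w²/12.

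- Time-stamped, readings every half day: 0.49 + 0.5²/12 = 0.511, SD 0.715.
- Whole dates, all first doses at the same clock time: 0.49 + 1/12 = 0.573, SD 0.757.
- Whole dates, first dose uniform over 10:00–22:00 (assumed): a further 0.5²/12, giving 0.594, SD 0.771.
- Whole dates with a full 24 h span required and reading times independent and uniform within ±2 h (assumed): three readings span 24 h only half the time, otherwise confirmation slips one half-day reading. This adds about 0.5² × 0.5 × 0.5 = 0.0625, giving SD 0.797 to 0.810.

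Simulation agreed, taking the event date as the date on which the 24 h is completed, control means of 2.5 to 4 days, and a first dose at noon, at 9 p.m. or uniform over 10:00–22:00. The SD was 0.713–0.719 time-stamped, 0.754–0.774 by date, and 0.792–0.809 by date with the strict span. The mean difference stayed at 0.49–0.51 day.

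**3. Power at 38 per group for a 0.5-day difference**

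| Measurement | SD | t test | Normal approximation |
|---|---|---|---|
| Exact time | 0.700 | 86.7% | 87.6% |
| Time-stamped readings | 0.715 | 85.3% | 86.2% |
| Dates, common first-dose time | 0.757 | 81.1% | 82.1% |
| Dates, spread first-dose time | 0.771 | 79.7% | 80.7% |
| Dates, strict span, ±2 h scatter | 0.79–0.81 | 75.7–77.7% | 76.8–78.8% |

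**4. The other branch.** If 0.7 already comes from date-counted data, power at 38 is 86.7% (t) or 87.6% (normal) and nothing is lost against plan. Removing rounding variance of 1/12 gives √(0.49 − 0.083) = 0.638 and power of 92.1% or 92.8%.

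**5. Gap rules.** The temperature windows are 07:00–11:00 and 19:00–23:00, so the shortest in-window gap is 11:00 to 19:00, 8 h. For RATs it is 11:00 to 07:00 next day, 20 h.

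- Constant clock times: no breaches.
- Steadily later times: total drift is capped at 4 h, which is 240/27 ≈ 9 minutes per reading over 28 temperature readings, or 240/13 ≈ 18 minutes per test over 14 RATs.
- Independent uniform times (assumed): each pair meets its minimum with probability 1/2, and three temperature readings meet both 12 h gaps with probability 1/6 ≈ 17%.

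**6. Consequence for RATs.** Negatives at 09:30 and then 09:00 next day are both in window but 23.5 h apart. They do not satisfy the outcome definition, so conversion waits for a later test, at least a day on.

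**The case against.** The strongest reply is that neither point threatens the trial, and much of it stands.

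- A reader might infer that the gaps cannot be met. They can: constant or slowly later reading times satisfy both. The rules are restrictive only for patients who use the tolerance in both directions.
- A reader might infer that the 12 h gap decides fever recovery. It does not. Recovery is confirmed by 24 h of normal temperature; the 12 h rule only spaces readings, and nothing says a reading at 11.5 h is void. Only the RAT outcome, which is secondary, carries its gap in the definition.
- A reader might infer that the trial is underpowered or biased. Date counting leaves the mean difference unchanged, and even where 0.7 describes exact time, power is close to the planned 80%. One reason is that 38 exceeds the 31–32 its own inputs require, though the article does not say the excess was meant to cover rounding.
- The article says only that the SD rests on previous studies, so whether it already contains rounding is unknown.
- The 50% and 17% figures need independent uniform reading times, for which the documents give no support.
- The 0.5-day argument does not reach RATs, which are done once daily and cannot resolve less than a day.

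What the reply does not remove is that the primary outcome's definition discards timing the schedule already provides, and that the RAT definition rejects pairs of tests taken on schedule.

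**Conclusion.** The point holds as a correction worth making, not as a flaw that undermines the trial. Whole-date counting of the primary outcome costs about 4 to 6 percentage points of power at 38 per group against time-stamped readings (about 85% down to 80–81%), and about 8 to 10 points if a strict 24 h span is enforced while reading times scatter over ±2 h. Those losses assume that 0.7 is the SD of the exact time. On the opposite assumption nothing is lost against plan and about 5 points could be gained. There is no bias either way.

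The gap rules conflict with the ±2 h windows. For temperature this is a compliance ambiguity. For RATs it can date conversion a day late for reasons unrelated to the patient, in anything from none of the pairs (constant testing time) to half of them (independent uniform times).

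**What to change.** 1. Record the clock time of the first dose and of every temperature reading and RAT.
2. Compute fever recovery in hours or half-days from the first dose to a stated reading of the confirmed normal run. Choose the first or the confirming reading before unblinding and write it down. Moving to the first reading changes the event itself, not only its resolution, so the choice should be explicit.
3. Define confirmation by consecutive scheduled readings: three normal temperature readings, and two consecutive daily negative RATs.
4. Set minimum gaps that fit the windows: 8 h between temperature readings and 20 h between RATs.
5. Align the 24 h wording in Assessment, Primary outcome and Secondary outcomes so that 24 h is nominal. Without this step, the gaps in item 4 would contradict those sections.
6. Leave RAT conversion in days.

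The cost is clock times in the diary, if it does not already collect them, and revised definitions. No visits, tests or patients are added. The drawback is that a nominal 24 h may be as short as 20 h (11:00 to 07:00 next day), which should be stated openly.
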